### 9.2. Secondary endpoints

- Toxicity: for each patient and for each type of toxicity, the worst degree suffered during treatment will be described.
- Objective response rate: defined as the number of complete plus partial responses divided by the number of patients enrolled.
- Progression free-survival: defined as the time from registration to progression or death without progression, whichever occurred first. Patients without progression at the end of the study will be censored at the date of the last visit when eventual progression was verified.
- Overall survival: defined as the time from registration to the date of death due to any cause. Patients still alive at the end of the study will be censored on the date of the last information on vital status.
- Metabolic response: defined as a reduction  $\geq 50\%$  of SUVmax after 2 weeks of treatment.

### 9.3. 1st stage analysis

According the two-stage design, the primary outcome will be evaluated within the first 17 patients and, if needed in order to assess study result, patients enrolment will be temporarily suspended. If 3 or fewer patients will be alive and without progression at 6 months, the study will be stopped early for futility.

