#### 4. STUDY DESIGN

This is a multicentre, single-arm, phase 2 study according to Simon's two-stage optimal design. This design has been applied to minimize the number of patients exposed to a possibly inactive drug, considering that alternative treatment options exist, although not satisfactory and likely to be more toxic. Patients who will receive at least one dose of study drug will be considered evaluable.

The primary endpoint will be the rate of evaluable patients alive and not progressed at 6 months.

The sample size calculation is based on the following statistical parameters:

- minimum acceptable rate of patients alive without progression at 6 months ( $p_0$ ) = 30%;
- auspicated rate ( $p_1$ ) = 50%
- type I and II errors = 10%.

According to these parameters, 22 evaluable patients should be enrolled at the first stage and the study will proceed to the second stage if at least 8 patients will be alive without progression after 6 months. At the second stage, further 24 evaluable patients will be enrolled for an overall sample of 46 evaluable patients. The study will be considered positive if at least 18 patients out of 46 will be alive without progression at 6 months. It is planned that 5 to 10 centres will participate in the study, which could be completed in 24 months.

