## 15. ETHICAL CONSIDERATIONS

### 15.1. Risk of undertreatment

The Simon's optimal two-stage study design has been chosen in order to minimize the number of patients exposed to a potentially inactive treatment, considering that alternative treatment options exist, although not satisfactory and likely to be more toxic. Moreover, an intensive schedule of response evaluation has been planned (6 and 12 weeks after treatment start) that allows to detect cases of early progression, with the aim of offering patients alternative treatment options.

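### Section 9.3 makes the stage-1 enrolment pause conditional, so stage-2 patients may be treated before the stage-1 verdict

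*Protocol*

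**What the plan says.** Section 4 (and the synopsis) describes a "single-arm, phase 2 study according to Simon's two-stage optimal design". Stage 1 has 22 evaluable patients. The trial goes on to 24 more if at least 8 of them are progression-free survivors at 6 months, and it is positive with at least 18 of 46. The reason given for the design is: "This design has been applied to minimize the number of patients exposed to a possibly inactive drug". Section 15.1 repeats it: the design was chosen "in order to minimize the number of patients exposed to a potentially inactive treatment".

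Section 9.3 describes the stage-1 analysis differently. It assesses the first 17 patients and stops for futility if 3 or fewer are progression-free survivors at 6 months. On enrolment it says only that "if needed in order to assess study result, patients enrolment will be temporarily suspended". There is no trigger, no decision-maker and no cap on entries while the result is pending.

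Section 9.1 counts progression, death, or stopping for toxicity followed by another antineoplastic treatment as a failure whenever it occurs within 6 months of registration. Section 7 schedules scans at weeks 6 and 12 and then every 3 months. On timing, Section 4 says only that the study is one "which could be completed in 24 months".

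**The concern.** The endpoint takes 6 months to observe. When the last stage-1 patient enters, many stage-1 outcomes are still unknown, and the full count comes 6 months later. A two-stage design limits exposure only if stage 2 does not start during that wait. A conditional pause with no trigger leaves this to judgement at the time.

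What is at stake is the property for which the optimal design was chosen, a small expected sample size when the drug is inactive. The error rates are not at stake.

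There is also a missed opportunity. Because failures count when they occur, the futility verdict is often settled before the last stage-1 patient reaches 6 months. Section 9.3 neither provides for acting on it then nor forbids it.

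**Working it through.** **Inputs.** From Section 4: p0 = 0.30, p1 = 0.50, both errors 10%, 22 then 24 patients, continue with at least 8, positive with at least 18 of 46. From Section 9.1: failures count at any time up to 6 months. Assumed, because the protocol gives no rate: 46 patients accrued without a pause over 18 to 24 months.

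**1. The plan's own design.** An exact binomial search for the optimal design (smallest expected N under p0, type I error at most 10%, power at least 90%) returns stop at 7 or fewer of 22, and reject with 18 or more of 46. This is the Section 4 rule.
- Type I error 0.0974; power 0.9049.
- P(stop at stage 1 | p0) = P(X ≤ 7 | n = 22, p = 0.30) = 0.671.
- E[N | p0] = 22 + (1 − 0.671) × 24 = 29.9.

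The figure 29.9 assumes that nobody enters between patient 22 and the verdict.

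**2. Entries during a 6-month wait with no pause.** Entries = monthly rate × 6.
- Accrual over 24 months: 46/24 = 1.92 per month; 6 × 1.92 = 11.5, or 48% of 24.
- Accrual over 18 months: 46/18 = 2.56 per month; 6 × 2.56 = 15.3, or 64% of 24.

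**3. Expected sample size with no pause.** E[N | p0] = 0.671 × (22 + entries) + 0.329 × 46.
- 0.671 × 33.5 + 0.329 × 46 = 37.6.
- 0.671 × 37.3 + 0.329 × 46 = 40.2.

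**4. When the futility verdict is fixed.**
- Section 4 needs 8 successes in 22, so it is fixed at failure 22 − 8 + 1 = 15.
- Section 9.3 stops at 3 or fewer of 17, so continuing needs 4; it is fixed at failure 17 − 4 + 1 = 14.

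**5. How much earlier the 15th failure is seen.** Simulation of 20,000 trials per setting, with constant hazard matched to the 6-month rate and progression found at weeks 6, 12 and about 26. At a true rate of 30%, among trials that stop, the verdict comes on average 3.0 months earlier (1.92 per month) or 2.5 months earlier (2.56 per month). At 3.83 per month (46 in 12 months) a similar simulation gave 2.0 months.

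**6. What each part of a remedy does.**
- Firm pause alone: no stage-2 entries before the verdict, so E[N | p0] returns to 29.9.
- Stopping at the 15th failure without a pause: at a true rate of 30%, about 5 (1.92 per month) to 9 (2.56 per month) stage-2 patients still enter on average, because many failures are seen only at the scan near 6 months.
- Both together: no extra entries, and an earlier verdict. In trials that proceed at a true rate of 50%, reopening at the 8th success shortens the pause by about 2.6 months (2.56 per month) or 1.7 months (3.83 per month).

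**7. Why the stage-1 rule must be settled first.** Joining 3 or fewer of 17 to the final rule of 18 of 46 gives P(stop | p0) = 0.202, type I error 0.117, power 0.945 and E[N | p0] = 40.1, even with a firm pause.

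**The case against.** The strongest reply is that the text already implies a pause. Its condition is that suspension is needed to assess the result, and while 6-month outcomes are pending that condition is arguably met. Section 4 also makes stage 2 follow from the stage-1 count. This stands in part: the overrun is permitted by loose wording, not planned. But a stopping rule that can be read as either optional or required does not protect the stated aim.

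A reader might infer that nearly all of stage 2 would be treated first: about 22 of 24 patients, with E[N | p0] near 44. The documents do not support that. Those figures need 46 patients in 12 months (3.83 per month). That rate fits a 24-month study only with a pause (12 + 6 pause + 6 follow-up); without one the trial would finish in about 18 months. Even *most of stage 2* fails at 48%. The 18-month end fits a 24-month study that includes the last follow-up (18 + 6), while 24 months of accrual would mean about 30 in total, but the protocol does not settle this.

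Two further objections stand. Once enrolment is paused, stopping at the 15th failure spares no patients; it only saves time. And unchanged error rates require final failures: Section 6.4 collects scans for possible revision of progression, and Section 5.3 provides for equivocal lesions awaiting confirmation.

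It may also be said that such mechanics belong in an analysis plan, which is not shown. That would apply if Section 9.3 were silent, but it sets a rule and leaves it open.

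**Conclusion.** The point holds as a weakness in wording that is cheap to repair. Section 9.3 allows enrolment to continue through the stage-1 wait, which would undo the benefit for which the optimal design was chosen. With no pause, and with 18 to 24 months of accrual assumed, about 11 to 15 of 24 stage-2 patients could enter before the verdict, and E[N | p0] would be about 38-40 instead of 29.9.

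The firm pause is what restores 29.9. Acting as soon as the verdict is fixed adds a decision about 2 to 3 months earlier at a true rate of 30%, under the constant-hazard and accrual assumptions. Type I error (9.7%) and power (90.5%) are those of the Section 4 rule. They stay the same because the trigger only brings forward the decision that the full count would give, provided the counted failures are verified as final.

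**What to change.** Reconcile the stage-1 rule between Section 4 (22 patients, at least 8) and Section 9.3 (17 patients, 3 or fewer). Then replace the conditional clause in Section 9.3 with three statements, given here with the Section 4 numbers:

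1. Enrolment pauses when the 22nd patient has taken a first dose, unless 8 successes are already recorded. The trigger is the first dose, not registration, because Sections 4 and 9 define evaluability by having taken the drug.
2. Enrolment reopens as soon as 8 of these 22 have reached 6 months alive and progression-free.
3. The trial stops for futility as soon as 15 of these 22 have a confirmed Section 9.1 failure. Under the present Section 9.3 numbers this would be 14 of 17.

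Say who confirms a failure before it counts, given the scan revision foreseen in Section 6.4.

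The cost is a few sentences and a running tally at the coordinating centre, which already collects the data centrally. The downside is that a pause becomes certain unless the successes are already recorded, which lengthens a trial that proceeds. At 2.56 per month and a true rate of 50%, the average pause would be about 6 − 2.6 = 3.4 months, so the 24-month estimate should be checked against it.

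### Section 9.3 gives a first-stage futility rule (17 patients, stop at 3 or fewer) that contradicts the rule in the Synopsis and Section 4 (22 patients, stop at 7 or fewer)

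*Protocol*

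**What the plan says.** Section 4 describes the trial thus: "This is a multicentre, single-arm, phase 2 study according to Simon's two-stage optimal design". The parameters are p0 = 30% ("minimum acceptable rate of patients alive without progression at 6 months"), p1 = 50% ("auspicated rate") and "type I and II errors = 10"%. The first-stage rule follows: "22 evaluable patients should be enrolled at the first stage and the study will proceed to the second stage if at least 8 patients" reach the 6-month endpoint. Then "further 24 evaluable patients will be enrolled for an overall sample of 46 evaluable patients", and the study is positive with 18 or more successes. The Synopsis gives the same figures.

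Section 9.3, which is devoted to the first-stage analysis, says that under the two-stage design "the primary outcome will be evaluated within the first 17 patients" and adds: "If 3 or fewer patients will be alive and without progression at 6 months, the study will be stopped early for futility".

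The only amendment listed concerns concomitant medications, so both rules are current text.

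**The concern.** Both the size of the first stage (22 against 17) and the stopping boundary (7 against 3) differ. A boundary of 3 in 17 is an observed rate of about 18%, well under the 30% that the plan treats as uninteresting. A boundary of 7 in 22 is about 32%.

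This is the trial's only go/no-go decision before the final analysis. The Synopsis, Section 4 and Section 15.1 justify the two-stage design by the wish to limit the number of patients given a possibly inactive drug when alternatives exist. A boundary that rarely stops the trial at 30% gives up most of that protection. With two rules in the text, the choice between them could also be made after the first-stage results are known.

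**Working it through.** **Inputs.** From Section 4 and the Synopsis: p0 = 0.30, p1 = 0.50, both errors 0.10; stage 1 n1 = 22, stop at r1 = 7 or fewer; total n = 46, positive at 18 or more (r = 17). From Section 9.3: n1 = 17, r1 = 3.

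**Formulas.** Let X1 ~ Bin(n1, p) be the first-stage successes and X2 ~ Bin(n − n1, p) the second-stage successes.

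- Probability of early termination: PET(p) = P(X1 ≤ r1).
- Probability of a positive study: the sum over x > r1 of P(X1 = x) × P(X2 ≥ r + 1 − x). This is the type I error at p = 0.30 and the power at p = 0.50.
- Expected sample size: EN(p) = n1 + (1 − PET) × (n − n1).

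**Step 1: reproduce the plan's design.** For 7/22 then 17/46:

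- PET(0.30) = 0.6713
- EN(0.30) = 22 + (1 − 0.6713) × 24 = 29.9
- type I error 0.0974, power 0.9049

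An exhaustive search over all two-stage designs with fewer than 60 patients returns this as the optimal design (smallest EN at p0) for 30%/50% and 10%/10%. The minimax design for the same inputs is 7/28 then 15/39. So Section 4 is internally correct, and 3/17 is the first stage of neither design.

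**Step 2: put the Section 9.3 rule in place of the Section 4 first stage, keeping 18 of 46.**

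| | 7/22, then 17/46 (Section 4) | 3/17, then 17/46 (hybrid) |
|---|---|---|
| Early stopping at p = 0.30 | 67.1% | 20.2% |
| Expected N at p = 0.30 | 29.9 | 17 + (1 − 0.2019) × 29 = 40.1 |
| Type I error | 9.74% | 11.66% |
| Power at p = 0.50 | 90.5% | 94.5% |

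For reference, a single-stage rule of 18 or more of 46 has type I error 11.8% and power 94.8%. The hybrid is close to having no interim look at all.

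**Step 3: how often the two rules disagree.** Section 9.3 says continue and Section 4 says stop when there are at least 4 successes in the first 17 and at most 7 in the first 22. At p = 0.30 the probability is 0.470. The opposite disagreement (3 or fewer in 17, yet 8 or more in 22) needs all five further patients to succeed and has probability 0.0003.

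**Step 4: both looks in sequence.** Stop at 3 or fewer of 17, then stop at 7 or fewer of 22, then 18 of 46: type I error 0.0973, power 0.9048. At p = 0.30, EN = 17 × 0.2019 + 22 × 0.4696 + 46 × 0.3285 = 28.9.

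**Step 5: where 3/17 would fit.** The same search for p0 = 20%, p1 = 40% and 10% errors returns 3/17 then 10/37 (type I error 0.0948, power 0.9033).

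**The case against.** The strongest reply is that the damage depends on which text is followed. Nothing gives Section 9.3 precedence. The Synopsis and Section 4 agree with each other and hold the parameters, the total and the final cut-off. A team that follows Section 4 runs a correct design, and one that applies both looks in turn loses almost nothing. That stands, and it rules out several stronger readings that a reader might infer:

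- *That the 10% type I error is lost outright.* It is exceeded only in the hybrid of Step 2, and then by 1.7 percentage points. It is 9.74% under Section 4 and 9.73% with both looks.
- *That the two rules cannot both be applied.* They act at different sample sizes, and both stop only for futility, so they can be run in sequence. What cannot be true is that each is the first stage of one and the same design. Section 9.3 does not offer the 17-patient look as an additional one, so this possibility does not resolve the conflict.
- *That power drops.* This would need the 24 second-stage patients to be added to 17, for a total of 41. The Synopsis and Section 4 fix the total at 46, and with that total the hybrid has higher power, not lower.
- *That the rule was carried over from a 20%/40% trial.* The numbers are consistent with that, but the protocol mentions neither those rates nor a total of 37. The origin is a guess.

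None of this removes the contradiction in the text.

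**Conclusion.** The point holds as a contradiction in the first-stage decision rule. Section 9.3 is the text that does not fit: the Section 4 rule is exactly the optimal design for the stated parameters, and 3/17 is not.

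The main consequence is lost futility protection. If Section 9.3 were followed alone, with 18 of 46 kept, and the true rate were 30%, the trial would stop early about one time in five instead of two times in three and would enrol about 10 more patients on average (40.1 − 29.9 = 10.2). The type I error of 11.7% is secondary and holds only under that same combination. The 47% rate of disagreement is also for a true rate of 30%.

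All figures assume independent binary outcomes and that the stopping boundaries are treated as binding. Because the conflict affects a go/no-go decision, it should be settled before any first-stage result is known.

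**What to change.** Amend Section 9.3 to match the Synopsis and Section 4: evaluate the primary outcome in the first 22 evaluable patients, and stop for futility if 7 or fewer are alive without progression at 6 months.

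The parameters p0 and p1, the error rates, the total of 46 and the final cut-off of 18 stay as they are. The cost is a one-sentence amendment, with no change to the planned sample size. Printing the exact operating characteristics beside the rule is optional; the alignment alone resolves the point.

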## 10. BIOMARKERS

### 10.1. Blood sample collection and analysis

Peripheral blood samples will be collected in EDTA tubes through 21G needles and stored as described below:

- at baseline (BL) (4 tubes)
- at day 14 of cycle 1 (C1) (2 tubes)
- at day 28 of cycle 1 (C2) (2 tubes)
- at the first restaging (R) (4 tubes)
- at progression of disease (PD) (4 tubes).

The following tests will be performed on blood samples but, given their uncertain values, these results will not be communicated to the patients and the treating physician:

- **Analysis of polymorphisms** in VEGF, VEGFR, CYP3A4 and UTG1A9 genes (at baseline only).  
Peripheral blood will be collected at BL in EDTA tubes through 21G needles, aliquoted and stored at -80°C. DNA from will be obtained using the DNA extraction kit (Qiagen/SABiosciences) following manufacturer instructions. The expression of the indicated polymorphisms will be evaluated by using pyrosequencing technology with specific 5'-biotinylated primers. Sequencing primers will be developed using SNP Primer Design software from Biotage. Genotyping will be done using a PyroMark ID pyrosequencer according to the manufacturer's instructions. Polymorphisms of these genes may affect activity and toxicity of treatment. One peripheral blood sample for each patient is adequate.
- **Analysis of CECs and CEPs** (at each of the above reported time-points).  
Peripheral blood will be collected, at all the time points previously described, in EDTA tubes through 21G needles and cell suspensions will be evaluated, after red cell lyses. Analysis of CEC/CEP should be performed within 24 h from collection of sample stored at 4 °C by flow cytometry. CECs are defined as negative for haematopoietic marker CD45, positive for endothelial markers P1H12. CEPs are defined as negative for haematopoietic marker CD45, positive for endothelial markers VEGF-R2 and positive for progenitor marker CD34. Vitality will be evaluated by staining with Syto 16.
- **Analysis of circulating angiogenic factors and cytokines** (at each of the above reported time-points).  
Peripheral blood will be collected in EDTA tubes through 21G needles aliquoted and stored at -80°C. The analysis will be done with the Bio-Plex™ technology.
- **Analysis of cfDNA mutations** (at each of the above reported time-points).  
Peripheral blood will be collected at BL in EDTA tubes through 21G needles, aliquoted and stored at -80°C. After Genome equivalent absolute quantification, samples will be processed using the *QIAamp Circulating*

*Nucleic acid Kit* (Qiagen/SABiosciences) according to manufacturer' instructionse and mutation analysis will be performed by BEAMing, Droplet digital PCR analysis or Next Generation Sequencing analysis.

- **Analysis of miRNA** (at each of the above reported time-points). Peripheral blood will be collected at BL in EDTA tubes through 21G needles, aliquoted and stored at -80°C. Samples will be processed using the *miRNeasy Mini kit* (Qiagen/SABiosciences) e enriched using the *RT2 qPCR-Grade miRNA Isolation Kit, MA-01* (Qiagen /SABiosciences). After miRNA retrotranscription as cDNA by the *RT miRNA First Strand Kit* (Qiagen/SABiosciences), miRNA expression will be measured using the *Human Serum RT miRNA PCR Array* (Qiagen/SABiosciences) that contains 85 sequences normally found in human serum and fluids, including those found altered in cancer patients.

## 10.2. Statistical analysis of biomarkers

Due to the small sample size, statistical analysis of biomarkers data will be conducted with the aim of hypothesis generation.

First of all, a complete description of data from biological and pharmacogenomic studies will be done. For biomarkers that might change over time as a consequence of treatment, levels before and after treatment will be compared with appropriate statistical tests, based on the type of data.

Outcomes of treatment will be compared between different VEGF and VEGFR phenotypes, with appropriate statistical tests.

P values  $\leq 0.05$  will be considered significant, and no adjustment is planned for multiple comparisons due to the exploratory nature of the analysis.

## 11. TUMOR METABOLIC EVALUATION

Our group has shown that early FDG-PET-CT is able to predict survival outcomes in colorectal rectal cancer (32). Therefore PET-CT scans are planned at:

- baseline (within 2 weeks before treatment start)
- 14 (+/- 2) days after treatment start.

Patients will be fasted for at least 6 hours and blood glucose level will have to be less than 150 mg/dL for the study to be eligible for further quantitative analysis.

PET images will be reconstructed using iterative reconstruction and normalized for injected dose and patient body weight. Image analysis will be performed utilizing a semi-automatic region-of-interest (ROI) drawing software package where a three-dimensional region will be drawn around the area of increased uptake. Threshold values will be adjusted in order to encompass the area of increased uptake visually.

For each tumor volume, the following parameters will be calculated:

- $SUV = (\text{measured activity concentration [Bq/mL]} / (\text{injected activity [Bq]} / \text{body weight [kg]} \cdot 1,000))$ .
  - o SUV-max = the maximum pixel value measured in the visualized lesion
  - o SUV-mean = the average activity values in the ROIs.
- TLG (Total Lesion Glycolysis) =  $SUV\text{-mean} \times \text{metabolic tumor volume (mm}^3\text{)}$

On the basis of these parameters, the following indicator will be calculated for each patients, in order to assess metabolic response:

- Highest SUVmax = the highest SUVmax value among all the evaluable lesions
- Total SUVmax = the sum of the SUVmax value of all the evaluable lesions
- Highest TLG = the highest TLG value among all the evaluable lesions
- Total TLG = the sum of the TLG value of all the evaluable lesions

PET response will be calculated by measuring changes reported at the post treatment examination (14 +/- 2 days after treatment start) compared to the baseline test. For all the indicators the change will be calculated as:

$$\Delta = (\text{value-post} - \text{value-baseline}) / \text{value-baseline} \times 100$$

Consistent with previous studies (32-34) the threshold to define a patient as responder according to change of SUV or TLG indicators is  $\leq -50\%$ . Therefore, patients with any change above these thresholds will be defined as non-responder. This value will be validated within this study for its predictive ability of survival outcome. Further thresholds will be eventually explored only in case of failure (lack of predictive ability) of the proposed validation.

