### **2.2. Secondary aims**

To describe:

- toxicity
- objective response rate
- progression free-survival
- overall survival.

To explore the prognostic and predictive value of:

- circulating endothelial (CEC) and progenitor (CEP) cells (at baseline and during treatment)
- circulating angiogenic factors (i.e. angiopoietin, sTIE, Ang-2, VEGF isoforms, PDGF, PlGF, sVEGF-R-1 and -2 isoforms)
- circulating cytokines profiling
- circulating miRNA profiling
- circulating free DNA (cfDNA) mutations
- VEGF, VEGFR, CYP3A4 and UTG1A9 polymorphisms
- early assessment of metabolic response with PET-CT scan.

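### Section 11 tests early PET against survival only through the -50% cut, with other cuts as the only stated fallback; a continuous analysis should be added alongside

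*Protocol*

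**What the plan says.** Among the exploratory secondary aims, section 2.2 lists the prognostic and predictive value of "early assessment of metabolic response with PET-CT scan". Scans are taken at baseline and at day 14 (± 2).

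Section 11 defines four indicators per patient (Highest and Total SUVmax, Highest and Total TLG). It gives one continuous measure for each: "For all the indicators the change will be calculated as" the percentage difference from baseline.

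It then moves to a binary classification. Citing earlier studies, it states that "the threshold to define a patient as responder according to change of SUV or TLG indicators is" a change of -50% or lower. All other patients form one group: "Therefore, patients with any change above these thresholds will be defined as non-responder". The use of the cut is stated next: "This value will be validated within this study for its predictive ability of survival outcome". The contingency follows: "Further thresholds will be eventually explored only in case of failure (lack of predictive ability) of the proposed validation".

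Section 9.2 repeats the dichotomy as a secondary endpoint, requiring a fall of at least 50% "of SUVmax after 2 weeks of treatment". It does not say whether this means Highest or Total SUVmax. No section states an analysis that relates the change, on its continuous scale, to PFS or OS.

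**The concern.** Once the change is cut at -50%, a patient at -48% counts the same as one at +40% and differently from one at -51%. If prognosis worsens gradually as the change becomes less favourable, most of that gradient is discarded. The loss is largest when few patients reach the cut. The protocol gives no expected responder share after 14 days of regorafenib alone. By their titles in the reference list, the three studies cited for the cut concern preoperative chemotherapy plus bevacizumab or preoperative radiochemotherapy, so they do not supply that share.

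The sample is at most 46 patients, and fewer if day-14 scans are missed, scans fail the fasting or glucose condition, or the trial stops after stage 1. The cut could then show no predictive ability although the measured change is prognostic. The stated response to that result, trying other cut-points, has the same weakness.

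**Working it through.** **Inputs from the protocol.** At most 46 evaluable patients (section 4); cut at -50% (sections 9.2 and 11); P ≤ 0.05 without multiplicity adjustment (section 10.2, written for blood biomarkers; assumed here to apply to PET and to be two-sided).

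**Inputs assumed.** Responder share p between 5% and 50%; a roughly normal change; log-hazard linear in the change; HR 1.5 per SD as an illustration.

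**The plan's own figure.** The protocol gives no sample size or power for PET. The 46 comes from the two-stage design in section 4. Exact binomial calculation (continue with at least 8 of 22, positive with at least 18 of 46) gives type I error 0.097 at 30% and power 0.905 at 50%. A search confirms it as the optimal design, so 46 is sound as a ceiling.

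**Efficiency of the cut.** Under the assumed model, with z the normal quantile at p and φ the normal density, the efficiency relative to the continuous change is φ(z)² / [p(1 − p)].

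| p | φ(z) | Efficiency | Loss | Equivalent of 46 patients |
|---|---|---|---|---|
| 50% | 0.3989 | 0.1592/0.25 = 0.637 | 36% | 29.3 |
| 30% | 0.3477 | 0.1209/0.21 = 0.576 | 42% | 26.5 |
| 20% | 0.2800 | 0.0784/0.16 = 0.490 | 51% | 22.5 |
| 10% | 0.1755 | 0.0308/0.09 = 0.342 | 66% | 15.7 |
| 5% | 0.1031 | 0.0106/0.0475 = 0.224 | 78% | 10.3 |

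The efficiency is highest at p = 50%. A loss of 36% is therefore the least that any single cut-point can achieve under this model, and moving the threshold cannot do better.

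**Power, by approximation.** Power = Φ(√(events × efficiency) × ln HR − 1.96). With 46 events and HR 1.5 per SD, the continuous analysis gives Φ(6.782 × 0.4055 − 1.96) = Φ(0.79) = 79%. The cut gives 59%, 55%, 49% and 36% at shares of 50%, 30%, 20% and 10%.

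**Power, by simulation of the Cox score test.**
- 46 patients, all with events: about 71% continuous, against 52%, 44%, 37% and 24% for the cut at the same shares.
- 46 patients, 50% progression-free at 6 months, censoring at 24 months (about 42 events; both assumed): 69–70% continuous, against 50%, 43%, 34% and 22%. With no effect, the rejection rate was 0.05–0.06 for the continuous test and 0.06–0.08 for the cut, so these figures do not understate the cut.

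**The opposite case.** If the hazard truly steps at -50% with HR 2.5 (same 24-month setting), the cut is better: 78%, 69%, 55% and 32%, against 58%, 50%, 37% and 20% continuous, at shares of 50%, 30%, 20% and 10%.

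For a smooth S-shaped effect centred on the cut, the squared correlation of each analysis with the true log-hazard shape shows which is better:

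| Logistic slope per SD | p | Linear term | Cut |
|---|---|---|---|
| 2 | 50% | 0.930 | 0.784 |
| 2 | 10% | 0.752 | 0.668 |
| 3 | 30% | 0.831 | 0.823 |
| 3 | 20% | 0.761 | 0.805 |
| 3 | 10% | 0.628 | 0.765 |
| 4 | 50% | 0.838 | 0.868 |

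At slope 3 the passage from 10% to 90% of the effect spans 2 × ln 9 / 3 ≈ 1.5 SD, which is not abrupt.

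**The case against.** A reader might infer that the protocol rules out a continuous analysis. It does not. In the sentence on further thresholds, the restriction concerns when new cut-points may be tried, not which analyses are allowed. The stated aim is broader than the cut, no survival model for PET is named, and a separate statistical analysis plan could add one. What remains is narrower: the protocol itself states the classification, its validation and the contingency after failure, and all three rest on cut-points.

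A reader might also infer that the -50% cut is the wrong test and should become purely descriptive. The documents do not support that. Testing a value fixed in advance is a legitimate question that only the cut can answer, and the same cut defines a secondary endpoint. That it comes from other treatment settings is a reason to validate it. As shown above, it can equal or beat a linear term when risk changes steeply near -50%, and the true shape is unknown.

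Nor is a loss of a third to two thirds a property of this trial. It depends on normality, a log-linear hazard and a 10–50% responder share, and at a 5% share the loss is larger still.

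Finally, section 9 calls all analyses descriptive, the PET aim is exploratory, and the day-14 result is withheld from patient and physician. This limits the weight of the point but does not remove it.

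**Conclusion.** The point holds in a limited form. The protocol computes a continuous change, states only the -50% cut as its survival analysis, and names only other cut-points as the fallback. Under a roughly normal change and log-linear hazard the cut loses 36% to 66% of the information for responder shares of 50% down to 10%, and 78% at 5%. Under the same model no alternative cut loses less than 36%. At an assumed HR of 1.5 per SD, the simulated loss of power is about 19 to 48 percentage points.

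If the effect is a step or steep near -50%, the cut is as good or better. The case is therefore for having both analyses, and for not reading a failed cut as absence of predictive ability. The matter concerns a secondary, exploratory aim. The primary endpoint, the stage rules and patient treatment are unaffected.

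**What to change.** In section 11:

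- Keep the pre-specified validation of the -50% value and the responder classification.
- Add alongside it a Cox model for PFS, and one for OS, on the continuous percentage change as section 11 already defines it, reporting the HR with its confidence interval. The percentage change is preferable to the logarithm of the post/baseline ratio, which is undefined if no uptake remains.
- Name one SUVmax indicator for this model, Highest or Total, and use the same name in section 9.2.
- State that lack of predictive ability will not be concluded from the cut alone, and put the continuous analysis in place of the search for further thresholds.

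The cost is a change of wording and one extra exploratory model per outcome on values already calculated, with no new scans, patients or visits. The added model is less powerful than the cut if the effect is a true step, which is why the cut is kept. The change should be made before outcomes are examined, because a continuous model introduced after a failed cut would look data-driven.
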